## Abstract

**Background:**

Optimal management of severe trauma patients with active hemorrhage relies on adequate initial resuscitation. Early administration of coagulation factors improves post-traumatic coagulation disorders, and four-factor prothrombin complex concentrate (PCC) might be useful in this context. Our main hypothesis is that four-factor PCC in addition to a massive transfusion protocol decreases blood product consumption at day 1 in severe trauma patients with major bleeding.

**Methods:**

This is a prospective, randomized, multicenter, double-blind, parallel, controlled superiority trial. Eligible patients are trauma patients with major bleeding admitted to a French level-I trauma center. Patients randomized in the treatment arm receive 1 mL/kg (25 IU/ml of Factor IX/Kg) four-factor PCC within 1-h post-admission while patients randomized in the controlled group receive 1 mL/kg of saline solution 0.9% as a placebo. Treatments are given as soon as possible using syringe pumps (120 mL/h). The primary endpoint is the amount of blood products transfused in the first 24 h post-admission (including red blood cells, frozen fresh plasma, and platelets). The secondary endpoints are the amount of each blood product transfused in the first 24 h, time to achieve prothrombin time ratio < 1.5, time to hemostasis, number of thrombo-embolic events at 28 days, mortality at 24 h and 28 days, number of intensive care unit-free days, number of ventilator-free days, number of hospital-free days within the first 28 days, hospitalization status at day 28, Glasgow outcome scale extended for patients with brain lesions on initial cerebral imaging, and cost of each strategy at days 8 and 28. Inclusions have started in December 2017 and are expected to be complete by June 2021.

**Discussion:**

If PCC reduces total blood consumption at day 1 after severe trauma, this therapy, in adjunction to a classic massive transfusion protocol, may be used empirically on admission in patients at risk of massive transfusion to enhance coagulation. Moreover, this treatment may decrease blood product-related complications and may improve clinical outcomes after post-traumatic hemorrhage.

**Trial registration:**

ClinicalTrials.gov NCT03218722. Registered on July 14, 2017

## Administrative information

The order of the items has been modified to group similar items (see http://www.equator-network.org/reporting-guidelines/spirit-2013-statement-defining-standard-protocol-items-for-clinical-trials/).

## Introduction

### Background and rationale {6a}

Severe trauma is the leading cause of mortality in young adults in developed countries and is the third cause of overall death in the USA [1]. Death occurs within the first 48 h among 87% of trauma patients with fatal outcome, and the first cause of death at 24 h is massive bleeding [2, 3]. Hemorrhagic shock is preventable with adequate strategies including early control of the active source of bleeding and an optimization of initial resuscitation called “damage control resuscitation” [4]. The concept of damage control resuscitation consists of a combination of early administration of blood products, control of post-traumatic coagulopathy, and a reduction of crystalloid infusion and maintaining permissive hypotension. This strategy aims at treating hypovolemia and coagulation disorders while avoiding dilution coagulopathy [4]. International guidelines for blood product administration recommend the transfusion of packed red blood cell (RBC) and fresh frozen plasma (FFP) as soon as possible with RBC/FFP ratio between 1:1 and 2:1 [5, 6].

Early administration of coagulation factors with FFP has been highlighted in the prehospital setting suggesting a potential beneficial effect on mortality [7]. However, FFP administration may be delayed due to logistical reasons such as transport and immediate availability. The administration of four-factor prothrombin complex concentrate (PCC) has emerged as an alternative to early administrate coagulation factors and is used to treat post-traumatic coagulopathy in diverse European countries [8, 9]. A strategy combining fibrinogen and four factor-PCC has decreased blood product consumption [8]. The reduction of blood product consumption is meaningful since blood transfusion is associated with post-traumatic infectious complications [10] and is a risk factor for multiple organ failure after severe trauma [11]. Recently, an open-label randomized controlled trial comparing a classic massive transfusion protocol to a tailored administration of procoagulant concentrates, including PCC and fibrinogen, also showed a decrease in RBC transfusion resulting in less patients requiring massive transfusion [12]. However, there is no randomized controlled double-blind study assessing the impact of PCC in addition to a classic massive transfusion protocol including fibrinogen administration and blood product transfusion with RBC and FFP [13].

The PROCOAG study therefore aims to test whether early administration of PCC allows a reduction of the total number of blood products transfused within the first 24 h after hospital admission of trauma patients with major hemorrhage.

### Objectives {7}

The primary objective of the PROCOAG study is to test whether the early PCC administration with standard blood products compared with standard care alone allows better control of post-traumatic hemorrhage, echoed by the total number of blood products transfused within the first 24 h after hospital admission.

Secondary objectives are as follows:
To conduct a separate analysis of the primary outcome:
Assessment of RBC consumptionEvaluation of FFP consumptionEvaluation of platelet consumptionTo compare between the two groups:
Time to normalize hemostasis defined by the time to achieve prothrombin time ratio < 1.5Time from admission to hemorrhage control defined during a surgical and/or radiological procedure, defined as the time necessary to control bleeding in the surgical field (operative field is dry without further foreseeable homeostatic procedures) or to control contrast blush after embolization during an interventional radiology (no more dye flushing).Thromboembolic events (pulmonary embolism, deep venous thrombosis)Morbi-mortality: mortality at 24 h and 28 days, intensive care unit (ICU)-free days (number of in-hospital days outside ICU) within the first 28 days, ventilator-free days during ICU stay within the first 28 days, hospital-free days within the first 28 days, and hospitalization status at day 28,Neurological outcome (Glasgow Outcome Scale Extended, GOS-E) for patients with brain lesions on initial scanTo evaluate differences in terms of cost-effectiveness

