#### Relevant concomitant care permitted or prohibited during the trial {11d}

From admission, all patients are managed according to European recommendations. Briefly, the source of bleeding should be identified as soon as possible and treated with emergency surgery and/or embolization following standard practice [16]. Regarding resuscitation, patients are treated in both groups with restricted volume replacement strategy, early transfusion of blood products with a RBC:FFP ratio between 1:1 and 2:1. Tranexamic acid (TXA) is intravenously administered within 3h after injury at a loading dose of 1 g infused over 10 min followed by an intravenous infusion of 1 g over 8 h [17]. Fibrinogen concentrate is administered in case of fibrinogen concentration <1.5 g/L [18] or viscoelastic evidence of a functional fibrinogen deficiency [19]. Platelets are administered to maintain a platelet count above 50 x 10^9^/L. Vasopressors can be infused in addition to fluids to maintain target systolic arterial blood pressure (>90 mmHg or >110 mmHg for head-injured patients). Blood samples are regularly drawn from admission to test hemostasis (prothrombin time ratio, Quick time, fibrinogen concentration, and viscoelastic tests where available), blood electrolytes, hepatic and renal function, and blood gases.

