#### Outcomes {12}

The primary outcome is the total number of blood products transfused within the first 24 h after hospital admission, including RBC, FFP, and platelets. The choice of this primary outcome is based on the following rationale. First, a recent randomized control trial exploring the effect of vasopressin use after severe trauma on the same endpoint [20], Second, even if transfusion is considered a pillar in the management of acute bleeding, blood products are associated with adverse events and poor clinical outcome [11, 21]. Third, mortality after severe trauma is a complex process depending on hemorrhage but also on traumatic brain injury and pre-existing medical conditions, specifically in elderly patients [22]. We thus believe that 24h total blood consumption is an accurate proxy of the severity of the bleeding until the hemorrhage stops.

Secondary outcome measures are (1) number of separate units (and volume) of RBC, FFP, and platelets and transfused in the first 24 h; (2) time to achieve prothrombin time ratio < 1.5; (3) time to hemostasis, defined as the time necessary to control bleeding in the surgical field (operative field is dry without further foreseeable homeostatic procedures) or to control contrast blush after embolization during an interventional radiology (no more dye flushing); (4) number of thrombo-embolic events at 28 days; (5) mortality at 24 h and 28 days; (6) intensive care unit (ICU)-free days (number of in-hospital days outside ICU) within the first 28 days; (7) ventilator-free days during ICU stay within the first 28 days; (8) hospital-free days within the first 28 days; (9) hospitalization status at day 28; (10) GOSE for patients with brain lesions on initial scan; and (11) cost of each strategy at days 8 and 28. Cost analyses will be performed on expensive care: blood products and procoagulant treatments administered, imaging exams, surgeries, and length of stay in each healthcare unit.

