#### Participant timeline {13}

All consecutive trauma patients admitted directly from the injury scene who require RBC transfusion with a risk of massive transfusion are screened on admission. Eligible patients are then rapidly enrolled by the study investigator. They should be randomized and treated accordingly within 60 min post-admission. After patient treatment, follow-up includes hourly visits until 6 h post-admission, as well as visits at 12 and 24 h to measure prothrombin ratio, assess hemorrhage control and monitor adverse events. Thrombo-embolic events are under special scrutiny during the entire hospital stay because they are frequently expected adverse effects of PCC treatment. Each suspicious thrombo-embolic event should be confirmed with venous Doppler echography or angiography and treated following standard practice. Thromboprophylaxis is left to physician discretion. Patients are followed for 28 days with the last visit aiming at collecting the Glasgow outcome scale extended (GOSE) for patients with brain lesions on initial cerebral imaging, mortality, and place of living (Fig. 1).

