##### Secondary outcome analysis

We will use the same strategy as for the primary endpoint in order to compare each quantity of RBC, FFP, and platelets, independently; i.e., a Student’s *t* test (if the application conditions are not met, we will use a non-parametric test).

Comparison by a Student’s *t* test (if the application conditions are not met, we will use a nonparametric test) of the values of the Quick Time between the two groups.

The delay between the time of the trauma and clinical hemorrhage control will be compared between the two randomization groups by a Student’s *t* test (if the application conditions are not met, we will use a nonparametric test).

The number of thromboembolic events at D28 will be recoded as a qualitative variable. At least one event (pulmonary embolism or deep vein thrombosis) will be required for this variable. It will then be compared using the chi^2^ test between the two groups (when the conditions for the application of the chi^2^ test are not met, the Fisher’s test will be used).

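### Time to hemostasis is defined only through a surgical or radiological procedure, so its planned comparison of randomized groups rests on a subset formed largely after randomization

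*Protocol article*

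**What the plan says.** Objectives {7} start the clock at admission and stop it at "hemorrhage control defined during a surgical and/or radiological procedure, defined as the time necessary to control bleeding in the surgical field", with loss of contrast blush as the radiological alternative. Outcomes {12} lists "time to hemostasis, defined as the time necessary to control bleeding in the surgical field" and gives the same two criteria: "operative field is dry without further foreseeable homeostatic procedures) or to control contrast blush after embolization during an interventional radiology (no more dye flushing".

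Two other sections speak more broadly. Participant timeline {13} states that "follow-up includes hourly visits until 6 h post-admission, as well as visits at 12 and 24 h to measure prothrombin ratio, assess hemorrhage control", without limiting this to patients who go to theatre or angiography. Secondary outcome analysis states: "The delay between the time of the trauma and clinical hemorrhage control will be compared between the two randomization groups by a Student’s" t test, or a nonparametric test if its conditions fail. Neither section says what counts as control when there has been no procedure.

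Whether a procedure takes place is a matter of care: the source of bleeding is "treated with emergency surgery and/or embolization following standard practice" (section {11d}).

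**The concern.** The definition gives the endpoint exactly two ways to occur, and both need a procedure. A patient whose bleeding stops with resuscitation alone, or who dies before a procedure is completed, has no value under it. The analysis is nevertheless described as a comparison of the randomized groups.

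Having a completed procedure is largely settled after randomization. A comparison restricted to patients with one no longer has the protection of randomization. If treatment alters who is in that subset, the two arms contribute different kinds of patient, and a difference in mean time may reflect that mix and not speed of hemostasis. At stake is the interpretation of the trial's timed clinical measure of bleeding control.

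**Working it through.** The article states no figure for this endpoint, so there is none to reproduce. The 162 patients per group in Sample size {14} concern the primary endpoint only.

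**1. The sections side by side**

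| Section | What it fixes |
|---|---|
| Objectives {7} | Control is read during surgery or radiology; clock starts at admission |
| Outcomes {12} | Dry field or no blush; no third route |
| Participant timeline {13} | Control assessed hourly to 6 h, then at 12 and 24 h; no restriction to procedures, no criterion |
| Secondary outcome analysis | Clinical control compared between randomized groups; clock starts at trauma |

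The first two restrict the endpoint to a subset. The last two read as if every patient contributes. The time origins also differ, a separate matter to settle in the same edit.

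**2. Can patients lack a value?** Yes. Eligibility {10} asks for a red cell transfusion and predicted massive transfusion (ABC score or physician judgment), not a procedure. The additional analyses section {20b} concedes that some patients without massive bleeding may be enrolled, and the Discussion expects that several may not need massive transfusion.

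**3. Is the subset formed after randomization?** Largely. Randomization and treatment are due within 60 min of admission. Some decisions to operate or embolize may come earlier, but a completed procedure, and survival to its end, will generally come later.

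**4. Direction of any bias.** Let a share p of controls have a procedure. Suppose PCC averts it in a share s of all patients and changes no individual time. Let m_s be the mean time in the averted patients and m_r the mean in the rest.

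- Control mean = [s × m_s + (p − s) × m_r] / p
- PCC mean = m_r
- PCC minus control = (s/p) × (m_r − m_s)

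With assumed p = 0.80, s = 0.10, m_s = 60 min and m_r = 130 min, the control mean is (0.10 × 60 + 0.70 × 130)/0.80 = 121.25 min and the PCC mean is 130 min, a difference of +8.75 min. With the two times exchanged (m_s = 130, m_r = 60), the control mean is (0.10 × 130 + 0.70 × 60)/0.80 = 68.75 min and the PCC mean is 60 min, a difference of −8.75 min. With s = 0 the difference is nil.

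**5. A simulated range.** All inputs are assumed: log-normal times with median 120 min and log-SD 0.6, 80% of controls having a procedure, no PCC effect on time, and procedures averted in the least severe patients first. Spurious mean difference (PCC minus control), by the correlation of severity with time:

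| PCC arm with a procedure | Correlation +0.3 | Correlation −0.3 |
|---|---|---|
| 80% | 0 min | 0 min |
| 75% | +1.9 min | −1.9 min |
| 70% | +3.8 min | −3.7 min |
| 60% | +7.8 min | −7.2 min |

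A negative correlation would arise if the most severe bleeds reach a procedure fastest. The article gives neither the procedure rate nor this correlation, so neither sign can be preferred.

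**The case against.** A reader might go further and infer that PCC is meant to spare patients a procedure, so that its successes drop out of its own arm and the bias runs against an effective drug. The article does not support this. It hopes for better hemorrhage control, enhanced clotting and fewer blood products; it nowhere says that PCC should avert procedures, and it gives no rate. The +8.75 min example has the adverse sign only because of the inputs chosen.

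The best case for the plan is this. An endpoint seen directly in the operative field or on angiography is precise. The clinicians who decide on a procedure are blinded. At 1 mL/kg and 2 mL/min, and assuming a weight of 50 to 100 kg, the infusion alone lasts 25 to 50 min, so many decisions may precede any drug effect. If PCC does not change who has a completed procedure, the arms stay balanced on this selection. The analysis section's broader wording may also mean that bedside assessments will be used, and the full protocol, eCRF guide or SAP may say how.

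Much of this stands. It limits the likely bias, and it rules out saying flatly that a patient without a procedure will never be scored. It does not remove the point. The definition is stated twice and is procedural both times, so this is not a detail left to another document. A later handling rule would still have to depart from that definition or keep the restriction.

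**Conclusion.** The concern holds in this form: the definition is confined to patients with a procedure, it does not match the visit schedule or the analysis wording, and as written it makes the comparison one of a largely post-randomization subset. Bias arises only if PCC changes who has a completed procedure, or who survives to its end, and may then go either way. Its size cannot be derived from the article; the figures above are illustrations on assumed inputs.

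The consequence is limited. This is one of eleven listed secondary outcomes, the sample size does not rest on it, and the primary conclusion is unaffected. The definition should still be corrected, because the change is cheap and without it a difference in either direction would be hard to interpret.

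**What to change.** Reconcile Objectives {7} and Outcomes {12} with Participant timeline {13} and Secondary outcome analysis, including the time origin, and state who contributes a value. Then:

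- Compare hemorrhage control in all randomized patients on one scale, the scheduled visits (hourly to 6 h, then 12 and 24 h), as a discrete or interval-censored time to control.
- Count a procedural dry-field or no-blush finding as control at the next visit.
- Treat death before control as a competing event.
- Report the exact procedural time descriptively, labeled as a non-randomized subset.

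One scale matters. Mixing exact procedural times with visit times would bring its own distortion: if 10% of one arm moved to visit times, rounding up could add as much as 0.10 × 60 = 6 min to that arm's mean with hourly visits, or 0.10 × 360 = 36 min across the 6 to 12 h gap. That is of the same order as the bias to be removed, or larger.

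The cost is coarser times and a short written criterion for control at the visits, which the article does not give. The visits are already scheduled and the investigating team is blinded, so no new assessment is needed.

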### Trial design {8}

The PROCOAG study is a therapeutic, prospective, randomized, multicenter, double-blind, parallel, superiority controlled clinical trial testing the efficacy of four factor-PCC to reduce the amount of blood products transfused in patients at risk of massive transfusion.

## Methods: participants, interventions, and outcomes

### Study setting {9}

Twelve French academic hospitals will participate in the study. All centers are level-I trauma centers receiving more than 200 trauma patients with an injury severity score (ISS)>15 each year. A list of all participating centers can be found on https://clinicaltrials.gov.

### Eligibility criteria {10}

#### Inclusion criteria

All consecutively admitted adult patients at risk of massive transfusion after severe trauma are screened for enrolment. Patients older than 18 years, admitted directly from the injury scene to a level-I trauma center, are eligible provided that they have two criteria: (1) a transfusion of at least one unit (U) of RBC prior to hospital admission or within the first hour after their admission (a delay of 90 min is tolerated if transfusion is decided within 1 h post admission) and (2) prediction by an assessment of blood consumption (ABC) score ≥ 2 [14] or by physician judgment of the need for a massive transfusion (defined by a transfusion of at least 10 RBC during the first 24 h or 3 RBC during the first hour).

#### Exclusion criteria

Patients are not eligible in the case of (1) traumatic cardiac arrest before randomization, (2) secondary admission from another health care facility/hospital (technical shortstops are accepted, i.e., such a stop should not 1 h before admission to the trauma center), (3) treatment with anticoagulants, (4) known pregnancy, (5) known hypersensitivity to four-factor PCC or its excipients, (6) patient with devastating injuries expected to die within the first hour post-admission, (7) patient under therapeutic limitation before randomization, (8) patient under guardianship, (9) knowledge of a contraindication to the use of NaCl 0.9% at the dose of 1 mL/kg (e.g., hyperchloremia or hypernatremia), or a drop-out criterion (10) inclusion in another trial within the last 30 days, (11) family or patient refusal, and (12) patient without health insurance.

### Who will take informed consent {26a}

Considering the study context, a considerable number of enrolled patients will be unable to consent (e.g., unconsciousness, agitation, post-traumatic stress). Informed consent can be therefore obtained from patient’s next of kin if present or consent is waived if no one is present at the time of enrolment, as authorized by French law in an emergency situation and approved by the ethics committee. This procedure was already used and authorized in a previous French study on trauma [15]. As soon as the patient’s next of kin is available and capable of informed consent in complete and faithful terms, consent is obtained. Informed consent must also be obtained from the patient whenever he/she becomes able to consent and up to 28 days after trauma. Patients and their next of kin have the right to refuse participation in the study or revoke their consent at any time. All information appears in an information notice and a consent form given to the subject. All these documents have been approved by the ethics committee. Written informed consent is obtained by the investigator. Two original copies are co-signed by both the investigator and the subject who consent.

